### Data collection

Informed by our previous longitudinal, multi-informant, and multi-site research with substance-involved mothers, data for the present study will be collected at three time points: pre-intervention, 12-, and 24-months after engagement in services. This longitudinal design will assess whether infant mental health improves and is sustained through a two-year period. The length of engagement in each of the intervention programs varies (mean length is 18 months with a range of 4 to 71 months) [52]. As such, some mothers will remain in the program for the duration of the study while others will not. The evaluation of primary and secondary outcomes will be similar for BTC and MWCHC, the only differences being that the HOME Inventory will not be applied at MWCHC. Data will be collected by the clinicians providing services onsite and by one CBR embedded at each site. The mothers’ clinical files will be reviewed by the CBRs to gather demographic data, addiction information, trauma and psychosocial risk information, treatments accessed, and treatment duration via retrospective file review. The CBRs will receive training on how to administer the MBQS and will be responsible for the in vivo observations and coding of the mother-child relationships. Participants who are no longer receiving services will be offered the opportunity to return to the intervention program for subsequent data collections, to complete the questionnaires over the phone, or to meet at a neutral location. Mothers will receive compensation for their time in the form of gift certificates to grocery stores at each time point.

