### Statistical analysis

All data analyses will be conducted in SAS and Mplus. For research question 1a, linear mixed models will be used to model the change in each of the primary outcomes from baseline to 24-months post-engagement for the BTC and MWCHC groups, controlling for demographic variables that potentially differ at baseline (e.g., maternal age, socioeconomic status, maternal ACEs). Slopes of the two groups will be compared using an interaction term. Linear mixed models can accommodate participants with missing observations [20]. For research question 1b, we will analyze secondary outcomes with a similar approach. For research question 1c, we will conduct regression analyses to predict which risk and protective factors identified at baseline predict change in the primary outcome for the BTC group.

For research question 2, we will conduct a series of mediation (indirect effects) and moderator analyses (interaction effects) for the BTC group, with time in treatment as the independent variable and infant mental health outcomes at 24 months as the dependent variable. Mediator (i.e., maternal behaviour, parenting attitudes, and maternal stress) and moderator (i.e., psychosocial risk) variables at 12 months will be used in all analyses.

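### Research question 2: with the outcome fixed at 24 months after engagement, time in treatment mirrors time since exit, so dose-response cannot be separated from loss of benefit after leaving

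*Protocol article*

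**What the plan says.** The Objective section words questions 2a and 2b in terms of treatment dose. Statistical analysis then fixes the exposure, the outcome time and the population: the models are run in the BTC group only, "with time in treatment as the independent variable and infant mental health outcomes at 24 months as the dependent variable". Mediators and the moderator are taken at 12 months.

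Data collection sets the clock. Assessments are made "pre-intervention, 12-, and 24-months after engagement in services". Length of engagement varies ("mean length is 18 months with a range of 4 to 71 months"), and the article accepts that "some mothers will remain in the program for the duration of the study while others will not". Mothers who have left can return, answer by phone or meet elsewhere, so their outcome is measured after exit. The clinical files supply "treatments accessed, and treatment duration via retrospective file review".

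The paragraph on research question 3 carries the mechanisms found under research question 2 into the theory of change and the decision model for SROI. That model covers potential lifetime impacts for the children.

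**The concern.** When the outcome time is fixed and counted from entry, the mother with the shortest stay is also the mother assessed longest after leaving. A mother with 6 months of service is assessed 18 months after exit. A mother with 24 months is assessed while in service or just as she leaves. A positive slope of the 24-month outcome on time in treatment could mean that each further month adds benefit. It could also mean that all mothers gained alike and the gain wore off after they left, or a mixture of the two.

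The article treats persistence as an open question: Data collection says the design is to show whether improvement lasts over the two years. The two explanations also have different consequences for SROI. A lasting gain that grows with service supports a long benefit stream, whereas a gain that fades after exit does not.

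**Working it through.** **The article's own figure.** Research question 2 has no stated sample size or power. The only figure is for research question 1a, and it reproduces: a noncentral t calculation with d = 0.70, 34 per group and two-sided alpha 0.05 gives 81.2% (stated 81.1%). Allowing for 30% attrition, 34 / (1 - 0.30) = 48.6, rounded up to 49 per group, so N = 98. Neither figure bears on the present point.

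**Inputs from the article.** Exposure: time in treatment, BTC only. Outcome: at 24 months, counted from engagement. (Question 1a in the Objective is worded as time after the intervention, but the visit schedule and the analysis both count from engagement.) Stay: mean 18 months, range 4 to 71, no SD given. Leavers are assessed.

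**Step 1, the identity.** Let T be the length of one continuous stay starting at engagement. Months in treatment by the visit = min(T, 24). Months since exit at the visit = max(0, 24 - T). Their sum is 24 for every T.

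**Step 2, what the regression can estimate.** With duration counted to the visit, the correlation between the two is -1.000, and the design matrix [1, dose, months since exit] has rank 2 of 3. The two effects have no separate estimates.

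**Step 3, if duration is not capped at 24 months.** The article does not say whether it is. Assume a shifted gamma stay (minimum 4, nominal mean 18, truncated at 71) with SD 8, 12 or 16; truncation brings the mean to 18.0, 17.8 and 16.9.

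| Assumed SD | Left before 24 months | Left before 12 months | Correlation, all mothers | Correlation, leavers | Variance inflation factor |
|---|---|---|---|---|---|
| 8 | 80% | 24% | -0.91 | -1 | 5.6 |
| 12 | 77% | 38% | -0.87 | -1 | 4.1 |
| 16 | 77% | 49% | -0.87 | -1 | 4.1 |

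The matrix now has full rank, but only because time in the programme after the outcome was measured counts as dose.

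**Step 4, two explanations with the same data.** Assumed effects: (A) a gain of 0.05 SD per month in treatment and no fade-out; (B) the same 1.2 SD gain for everyone, with 0.05 SD lost per month after exit.

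| Months in treatment | 4 | 8 | 12 | 16 | 20 | 24 |
|---|---|---|---|---|---|---|
| A: 0.05 × dose | 0.2 | 0.4 | 0.6 | 0.8 | 1.0 | 1.2 |
| B: 1.2 - 0.05 × (24 - dose) | 0.2 | 0.4 | 0.6 | 0.8 | 1.0 | 1.2 |

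**Step 5, does the 12-month outcome help?** At 12 months, A gives 0.2, 0.4, 0.6, 0.6, 0.6, 0.6 and B gives 0.8, 1.0, 1.2, 1.2, 1.2, 1.2. They differ by a constant 0.6 SD, which a free visit effect absorbs. With both visits stacked, [1, dose to date, months since exit] has rank 3 of 3; adding a visit effect gives rank 3 of 4.

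**Step 6, how large a slope fade-out alone could give.** Assume a 0.7 SD gain for every mother while in service, decaying after exit with a half-life of 6 or 12 months, and a stay of mean about 18 months (4 plus an exponential, or a lognormal, limited to 4 to 71). The slope is 0.30 to 0.40 SD per additional 12 months if duration is capped at the visit, and 0.13 to 0.19 SD if it is not.

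**The case against.** The best reply is that the slope is not an error. If benefit fades after exit, children of mothers who stayed longer really are better off at 24 months, and the effect of duration on a fixed-time outcome properly includes that route. This stands. A reader might infer from Step 6 that the planned regression produces a spurious dose effect or inflates the type I error. The documents do not support that: the Objective asks about associations with dose, an association does exist in that scenario, and detecting it is power. What is lost is the ability to say why it exists.

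The word exactly also depends on a definition that the article leaves open. Duration might be counted past month 24, and attendance might be interrupted or start after the engagement date. Each loosens the identity for some mothers. With one continuous stay it remains exact among leavers, and the article describes no handling of the other cases. A detailed definition may sit in a document not shown, but the article already fixes duration as the exposure and 24 months as the outcome time, and with those two choices no added covariate separates the explanations for leavers.

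It can be said that the second visit helps. It does if no free visit effect is fitted, or if MWCHC is used to supply the time trend under a common-trend assumption. The article plans neither for research question 2, which is confined to BTC and to the 24-month outcome.

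Finally, a reader might infer that the mediators would show the same pattern. This was not calculated and does not follow. They are measured at 12 months, when a mother still in service has had no time to lose benefit after exit, so it could concern only those who left before 12 months.

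**Conclusion.** The concern holds as a limit on interpretation. The planned slope is a valid net association of longer stay with status at 24 months. It cannot separate dose-response from loss of benefit after exit. For mothers with one continuous stay who leave by month 24, the two variables are the same variable with the sign reversed. Over all mothers the correlation is -1 if duration stops at the visit and about -0.87 to -0.91 otherwise.

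Under the assumed stay distributions, 77% to 80% of mothers have left by 24 months, so most of the BTC group is affected. These shares rest on assumed shapes and SDs, because the article gives only the mean and range. The effect sizes and half-lives in Steps 4 and 6 are illustrations. Research question 2 is secondary and unpowered, and the primary comparison is untouched. The point still deserves a change because the article speaks of dose and sends the mechanisms into a lifetime economic model.

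**What to change.** 1. Keep time in treatment as the exposure, and state whether it is counted only to the 24-month visit.
2. Describe the result for research question 2 as a contrast between mothers still or recently in service and mothers who left earlier. Draw no dose-response or persistence conclusion from it.
3. Carry no such conclusion into the SROI model, except as a sensitivity scenario run with and without fade-out after exit.
4. Where the file review records service contacts, add a sensitivity analysis, not a replacement, using contacts received by a fixed cut-off, with and without months since last contact. For a continuous stay, months since last contact largely fixes duration. The adjusted model therefore estimates intensity of service at a given duration and should be labelled so; it does not recover the effect of staying longer.

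The cost is a few sentences of analysis wording, one extra scenario in the economic model, and counting contacts in a file review that is already planned. The downsides are a weaker dose statement and dependence on how completely contacts were recorded: the article lists treatments accessed and does not promise counts.

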### Objective

This paper describes the protocol for a comparative effectiveness study of the Breaking the Cycle (BTC) and Maxxine Wright Community Health Centre (MWCHC) intervention programs offered to substance-involved mothers and their young children (0–6 years). This study will explore the effectiveness of the mother-child focused BTC intervention as compared to the mother-focused program of the MWCHC program. More specifically, the study aims to establish the comparative effectiveness and mechanisms of change of the infant mental health components at BTC, as well as estimate the long-term social return on investment (SROI) of BTC. The key research questions it aims to answer are:1a: Do children at BTC demonstrate enhanced infant mental health compared to children at MWCHC up to 2 years post-intervention?1b: Are decreases in exposure to child ACEs, maternal stress, and mental health symptoms and increases in environment scores, parenting attitudes, and mother-child relationship scores greater among mothers at BTC than at MWCHC between pre-treatment and 24-months after engagement?1c: Are lower exposure to psychosocial risk, lower maternal mental health difficulties, and lower maternal stress at baseline associated with enhanced infant mental health scores over time?2a: Are the associations between treatment dose and infant mental health scores mediated by parenting attitudes and the quality of the mother-child relationship?2b: Does child exposure to psychosocial risk moderate the association between treatment dose and child outcomes?3: What is the estimated long-term SROI of the combined mother-child focus and infant mental health components of the BTC program?

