### Participants

Participants will comprise substance-involved pregnant and/or parenting women with children between the ages of 0–6 years old. We aim to recruit a total of 100 participants: 50 through the BTC intervention and 50 through the MWCHC intervention. To be eligible for the study, participants must: be receiving services at either BTC or MWCHC; have a child under the age of 6 years; and be able to complete the study questionnaires in English. There are no exclusion criteria for participation in this study.

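### Research question 2a counts time in treatment with no cut-off while its mediators are measured at month 12, so for mothers who stay longer part of the exposure follows the mediator

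*Protocol article*

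**What the plan says.** The question is put in the Objective section: "Are the associations between treatment dose and infant mental health scores mediated by parenting attitudes and the quality of the mother-child relationship". The Statistical analysis section then names each part of the model.

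- **Population:** BTC only. "we will conduct a series of mediation (indirect effects) and moderator analyses (interaction effects) for the BTC group".
- **Exposure and outcome:** "with time in treatment as the independent variable and infant mental health outcomes at 24 months as the dependent variable".
- **Mediators and moderator:** "variables at 12 months will be used in all analyses".

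The Data collection section describes the exposure. For length of engagement, "mean length is 18 months with a range of 4 to 71 months", and "some mothers will remain in the program for the duration of the study while others will not". Community-based researchers extract "treatments accessed, and treatment duration via retrospective file review". No section says up to which date treatment is counted. The baseline covariates listed under Statistical analysis belong to research question 1a (1b follows a similar approach). None is named for research question 2.

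**The concern.** A mediation analysis needs exposure, then mediator, then outcome. The outcome at month 24 and the mediators at month 12 respect that order. The exposure does so only up to month 12. If a mother's full duration is entered, the exposure-to-mediator path regresses a 12-month score on months of treatment that had not yet happened. For stays beyond month 24, some of the exposure also follows the outcome.

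This matters if staying depends on how things are going. If lower stress or better parenting attitudes at month 12 make a mother more likely to remain, that path is non-zero even when treatment does nothing to the mediator. Multiplied by a real mediator-outcome association, it yields an apparent indirect effect. The Statistical analysis section carries the mechanisms found under research question 2 into the theory of change for the social return on investment (SROI), so an effect of the mediator on retention could be modelled there as the way the programme works.

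**Working it through.** **1. The plan's own figure.** The only power statement concerns research question 1a: d = 0.70, 34 completers per group, 81.1% power. A noncentral t calculation gives 81.2%, and 34 / (1 - 0.30) = 48.6, so 49 per group and N = 98. It reproduces and is not touched by this point. No figure is stated for research question 2. Its sample is one arm ("50 through the BTC intervention and 50 through the MWCHC intervention"), so 50 x (1 - 0.30) = 35 BTC mothers with complete data.

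**2. How much exposure falls after the mediator.** The documents give only a mean of 18 and a range of 4 to 71 months; the shape is assumed. With stay T = 4 + an exponential variable of mean 14:

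- P(T > 12) = exp(-8/14) = 56.5%.
- P(T > 24) = exp(-20/14) = 24.0%.
- Mean months after month 12: 14 x 0.565 = 7.9, and 7.9 / 18 = 44% of all months.
- Capped at month 24: 14 x (0.565 - 0.240) = 4.55 months after month 12, out of 4 + 14 x (1 - 0.240) = 14.64, so 31%.

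Gamma shapes with the same minimum and mean, and SD 8, 12 or 16, give 76%, 62% or 52% past month 12.

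**3. What that does to the indirect effect.** Simulation with no effect of treatment on the mediator or the outcome, mediator-outcome correlation 0.5, n = 35 and 3,000 replicates per cell. Each SD of better 12-month mediator multiplies the leaving hazard *after month 12* by the ratio shown. The indirect effect is declared when both paths have p < 0.05.

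| Hazard ratio per SD | Uncapped time | Capped at 24 | Cut at 12 |
|---|---|---|---|
| 1 (no selection) | 4.0% | 4.1% | 4.4% |
| 0.7 | 14.4% | 6.0% | 4.3% |
| 0.5 | 35.4% | 12.0% | 4.0% |

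A second model was run with selection expressed as a change of 0.3, 0.5 or 0.8 in log mean later stay per SD, and a Monte Carlo interval for the product of the paths. At n = 35 it gives 12%, 24% and 41% uncapped, 6.7%, 10.5% and 17.5% capped at 24, and about 5% cut at 12. At n = 1000 the uncapped rate is 100% for all three values, so this is bias and not small-sample noise. With a weaker mediator-outcome correlation (0.3, selection 0.5, n = 35) the rates are 8.8% uncapped and 2.4% cut at 12.

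**4. What the cut does not repair.** Step 3 switches selection on only after month 12, so a 12-month cut removes it by construction. Stays can end from month 4. Letting the same hazard ratio act from month 4, with the mediator treated as a persistent trait, gives at ratio 0.5 about 70% uncapped, 67% capped at 24 and 52% cut at 12. Adjusting for the baseline mediator as well (assumed correlation 0.6 with the 12-month value) brings the last to 31%. At ratio 0.7, the 12-month dose gives about 19%, or 11% with that adjustment, against 31% for time capped at 24.

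**The case against.** The strongest reply is that the article never says *total* time. It says time in treatment and, in the Objective section, treatment dose. The window for counting it could be set in an analysis plan that is not shown, and the deliberate month-12 and month-24 spacing suggests that time order was intended. This has weight: such a plan could define a 12-month dose. But the article does fix the exposure and the mediator month, and the duration it takes from the files averages six months more than the mediator visit allows. An analyst who follows the text literally would fit the overlapping model.

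Three stronger readings are tempting and are not supported.

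- *The exposure comes after the mediator.* It does not. Treatment starts before month 12, and under the exponential assumption about 43% of mothers have all of theirs by then. The defect is partial overlap.
- *A false mechanism will be found about a third of the time.* The 35% cell needs strong selective staying and time counted past the end of follow-up. Capped at month 24, the same model gives 6-12%. The documents give no evidence that mothers who are doing better stay longer; those with greater need might.
- *Cutting dose at month 12 restores the nominal error rate.* It does so only if leaving before month 12 is unrelated to the mediator, as step 4 of the working shows.

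**Conclusion.** The point holds as one of partial overlap. As written, research question 2a lets exposure accrue after the mediator for roughly 52-76% of mothers, depending on the assumed stay distribution. That can create a false indirect effect if 12-month scores influence staying. Under selection confined to the period after month 12, the error rate is about 14-35% uncapped and 6-12% capped at month 24, against about 4% with a 12-month dose. The strength of selection, the mediator-outcome correlation and the stay distribution are assumptions; without selective staying there is no inflation.

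Severity is should-fix. The analysis is secondary, single-arm and unpowered, and it is one input among several to the SROI theory of change. Research question 1 and the sample size stand as they are. A reader might infer that the trial's main comparison is compromised; nothing in the document supports that.

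**What to change.** - **Research question 2a:** define dose as treatment received from entry to the 12-month assessment. Keep the mediators at month 12 and the outcome at month 24. Adjust the mediator and outcome models for the baseline mediator and the baseline outcome.
- **Total dose-outcome association and research question 2b:** count no treatment after the date of the outcome assessment.
- **Reporting:** describe the research question 2 indirect effect as associational, including where it enters the SROI theory of change.

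The cost is a few lines of analysis text and dated extraction from files already being reviewed. There are two downsides. Months capped at 12 vary less, since over half of mothers may share the maximum value; contacts, from the record of treatments accessed that is already extracted, can serve as a supporting dose measure, though they are not the same exposure as time. And the cut restores time order without removing selective leaving before month 12, which is why the baseline adjustment and the associational wording are needed as well. The window should be fixed before the data are analysed.

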### Recruitment

Mothers will be invited to participate in the study by BTC and MWCHC clinicians providing services at the community-based intervention programs. The clinicians will introduce the research to potential participants within six weeks following their first intake meeting and before receiving any services (e.g., counselling, group participation). Women will be assured that whether they participate or not in the study will not affect the clinical services they receive at either program. This lag time is essential to build trust and rapport with the mothers [23]. Mothers who are interested in participating in the research will be contacted by a community-based researcher (CBR), embedded within each of the intervention programs, who will further explain the research and ask for consent to participate, to be contacted for follow-ups, and to access their clinical file to obtain demographic and other information about psychosocial risk exposure through a retrospective file review. This is a trauma-informed approach to obtaining information whereby participants are not obligated to report information that they have already shared clinically [23].

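### The RQ2 mediators are fixed as 12-month values with no baseline term, so if length of stay depends on a mother's starting level, the indirect effect partly reflects who stays

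*Protocol article*

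**What the plan says.** RQ2a in the Objective section asks: "Are the associations between treatment dose and infant mental health scores mediated by parenting attitudes and the quality of the mother-child relationship". The Statistical analysis section answers it with tests of indirect effects and of interactions, run in BTC mothers only. These models are set up "with time in treatment as the independent variable and infant mental health outcomes at 24 months as the dependent variable". The mediators listed there are "maternal behaviour, parenting attitudes, and maternal stress", and the mediator and moderator "variables at 12 months will be used in all analyses". No baseline value, change score or other covariate is named for RQ2. The same section does name baseline terms elsewhere: covariates for RQ1a (with a similar approach for RQ1b) and baseline predictors for RQ1c.

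A baseline is planned. Under Data collection, "data for the present study will be collected at three time points: pre-intervention, 12-, and 24-months after engagement in services". Under Recruitment, the study is introduced "within six weeks following their first intake meeting and before receiving any services". Data collection also shows that length of stay varies widely ("mean length is 18 months with a range of 4 to 71 months") and that some mothers will leave while others stay on.

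**The concern.** The stated purpose of RQ2 is to show how the BTC programme brings about change. A 12-month level is not a change. It carries forward whatever level the mother had on entry, because parenting attitudes, stress and observed behaviour are partly stable.

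Time in treatment is decided by circumstances and by the mothers themselves, and the analysis has one arm, so no comparison group protects the path from treatment to mediator. Two patterns of selection are possible:

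- If mothers who enter with better scores stay longer, that path is non-zero even when the programme changes nothing, and a pre-existing difference looks like a mechanism.
- If mothers with greater need stay longer, the sign reverses, and a true mediated effect can be masked.

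The maternal stress questionnaire and both child questionnaires are completed by the mother. A stable maternal characteristic could therefore plausibly run through to the 24-month outcome as well. RQ2 findings are also one input to the theory of change behind the social return on investment work.

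**Working it through.** **Plan's own figures.** The article gives no figure for RQ2. Its only calculation is for RQ1a, and it reproduces: a two-sided two-sample t-test with d = 0.70 and 34 per group has power 0.8116 (stated 81.1%), and 34 / 0.70 = 48.6, rounded up to 49 per group. From there I take only the attrition: 50 BTC mothers × 0.70 = 35 with complete data.

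**Assumed inputs** (none is in the documents; all variables standardized):
- r = correlation of length of stay with the baseline mediator, 0 to 0.4 in absolute value
- s = stability of the mediator from baseline to 12 months = 0.6
- b = correlation of the 12-month mediator with the 24-month outcome = 0.4
- true effect of treatment on the mediator = 0

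**Size of the spurious effect.** Without the baseline mediator, the treatment-to-mediator path has expectation r × s, and the indirect effect r × s × b.

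| absolute r | first path, r × s | indirect effect, r × s × b |
|---|---|---|
| 0 | 0 | 0 |
| 0.2 | 0.12 | 0.048 |
| 0.3 | 0.18 | 0.072 |
| 0.4 | 0.24 | 0.096 |

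A negative r gives the same sizes with a negative sign. A check with n = 200,000 gave 0.047, 0.072 and 0.097 for r = 0.2, 0.3 and 0.4 unadjusted, and about 0.000 with the baseline mediator in both equations.

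**False detection at n = 35** (3,000 simulated studies per setting, r = 0.2 to 0.4). Without the baseline term, the first path was significant in 11% to 28% of studies and both paths in 7% to 17%. With it, the rates were about 5% and 2%. A negative r gives the same rates, since it only flips the sign of the first path and the tests are two-sided.

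**Second set of assumptions** (b = 0.5, s = 0.5 to 0.7, n = 35, 2,000 runs each), both paths significant:

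| r | without baseline mediator | with baseline mediator |
|---|---|---|
| 0 | 3% to 5% | 2% to 4% |
| 0.2 | 9% to 11% | 2% to 4% |
| 0.3 | 13% to 19% | 2% to 3% |
| 0.5 | 25% to 44% | about 3% |

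**Precision.** The ratio of the first-path standard error with the baseline mediator to that without it is about √[(1 − s²) / ((1 − r²)(1 − r²s²)) × 33/32].
- r = 0: √(0.64 × 33/32) = 0.81
- r = 0.2: √(0.64 / (0.96 × 0.9856) × 33/32) = 0.84
- r = 0.4: √(0.64 / (0.84 × 0.9424) × 33/32) = 0.91

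So the standard error falls by about 9% to 16% for r between 0.4 and 0.2. It falls by just under a fifth at r = 0, where there is no bias to remove (simulated: 0.175 to 0.143).

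**What adjustment leaves behind.** The clean zero depends on a baseline mediator measured without error. Take reliability 0.8 (assumed), observed r = 0.3 and observed s = 0.6. The unadjusted first path is 0.3 × 0.6 / 0.8 = 0.225. The adjusted path is (0.225 − 0.3 × 0.6) / (1 − 0.3²) = 0.045 / 0.91 = 0.05, so about a fifth of the bias remains.

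**The case against.** The strongest reply is that the sentence fixes when the mediator is measured, between entry and the 24-month outcome, and says nothing about covariates. Covariate lists for a mediation model are often left to a full analysis plan, and a plan that added baseline mediators would contradict nothing in the article. This stands in part. A reader might infer that baseline adjustment has been ruled out, and the text does not support that. But the article does fix the mediator as a 12-month value in every RQ2 analysis and names baseline terms for RQ1 only. An analysis that follows it as written would have the weakness.

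The size rests wholly on assumed correlations. This stands. Nothing in the documents says that better-functioning mothers stay longer. Selection could run the other way or be absent, and at r = 0 there is no bias.

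The remedy has limits, and these stand too. Measurement error and other reasons for staying remain. Mean stay is 18 months, so part of the exposure can come after the 12-month mediator, and a baseline covariate does not cure that. Baselines may be missing for some women: observed maternal behaviour needs a mother-child interaction, and two of the three stress domains concern the child. Eligibility also requires a child under six, so the number affected is unclear.

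Finally, RQ2a asks about associations, and RQ2 informs a theory of change developed with the Steering Committee. A reader might infer that a biased RQ2 coefficient enters the benefit-cost ratio, but the article does not say that any does.

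**Conclusion.** The point holds as a conditional weakness worth correcting. With 12-month mediator values, no baseline term, one arm and an unassigned exposure, the indirect effect mixes change with pre-existing differences whenever length of stay is related to the mediator's starting level. Under stability 0.6, mediator-outcome correlation 0.4 and a stay-baseline correlation of 0 to 0.4 in absolute value, the spurious part is 0 to about 0.10 SD in absolute size, in the direction of selection.

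A reader might go further and conclude that RQ2 will report a false mechanism, or that baseline adjustment would make the estimate causal. The documents support neither. They do not show that stay is related to baseline levels, and adjustment deals with only one of several routes of confounding. The case for the change does not need the stronger reading: the baseline measures are already scheduled, and at the assumed stability they sharpen the first path even if there is no selection.

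**What to change.** Add to the RQ2 paragraph of the Statistical analysis section, in the authors' own wording:

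- In each RQ2a model, the pre-intervention value of the same mediator is a covariate in both the mediator equation and the outcome equation, and the indirect effect is reported from that model.
- Baseline values missing for women pregnant at intake are handled by the missing-data method used in the model, and those women are not dropped.
- Adjustment reduces but does not remove confounding, because measurement error and other reasons for staying remain. The indirect effect is therefore described as an association.

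The cost is a few sentences of text, one degree of freedom per equation in a sample of about 35, and some missing baseline values, chiefly for maternal behaviour and parenting stress. No new measure or visit is needed.
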